## 17 Statistical methods

### 17.1 Sample size

The trial will use a stratified design with one strata for primigravidae and secundigravidae and one strata for multigravidae. It is designed to detect a 25% reduction (RR 0.75) in composite adverse birth outcomes (SGA, low birth weight and pre-term birth) in women in their first and second pregnancies with an 90% power and a 2-sided significance level of 0.05, if the rate of placental malaria in the IPT-SP group is similar to that found ongoing observational studies of women receiving routine care in the same area of Malawi. The proposed difference is based on four previous trials of IPTp which jointly reduced low birth weight by 29%. Thus the efficacy of ISTp is expected to be similar to the efficacy of IPTp before the emergence of widespread SP resistance. In the ongoing IPT-mon study in Malawi, the incidence of SGA, low birth weight or preterm birth was 40.3% (N=494) ([name], personal communication). Therefore the study is designed to detect a 25% difference between 40.3% in the control (IPTp) group and 30.2% in the intervention (ISTp) group.

This would require 491 participants in each arm or 982 in total. To allow for a 15% loss to follow-up, 1155 women in their first and second pregnancies will be recruited. This sample size would also have an 81% power to detect a 25% or greater reduction in placental malaria (active or past infection), with a significance level of 0.05. If a power of 80% is used, the study can detect a difference of 21.8% or greater in the primary endpoint. If the incidence is 33.3% instead of 40.3% the study still has 80% power (instead of 90%) to detect a 25% reduction.

The trial is also designed to detect a 50% reduction in past or present placental malaria infection at delivery in multigravidae, based on previous studies of IPTp, assessed by placental histopathology and RDT. The current rate in women in Malawi who are taking IPTp-SP is estimated from IPT-mon at 20.5% ([name], personal communication). A reduction by 50% to 10.25% will require 213 women per arm or 426 in total. To allow for a 15% loss to follow-up we will recruit 500 multigravidae.

The total sample size will therefore be  $1155 + 500 = 1655$ .

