### 17.3.3 Efficacy

The primary efficacy analysis will be the assessment of the superiority of ISTp-DP over IPTp-SP in women in their first and second pregnancies for the prevention of any of the following: SGA, pre-term birth or low birth weight. Similar analyses will be undertaken for the additional primary outcome of evidence of active or recent infection assessed at delivery by placental histopathology and RDT in women in their third to fifth pregnancies, and for the secondary efficacy outcomes. Impact will be determined by gravidity strata as the primary analysis. As a secondary analysis we will also estimate the overall estimated effect, extrapolated to all gravidity groups using a weighted analysis providing extra weight to the observations in multigravidae so that the final estimate represents the distribution of gravidity groups in the population attending antenatal clinics (based on antenatal clinic records).

Generalised linear models will be used where appropriate to assess the effect of the intervention according to different characteristics of the participants. Treatment effects will be expressed in terms of relative risk and risk difference for dichotomous variables and mean difference for continuous variables, and the corresponding 95% confidence intervals. Superiority will be defined as a positive treatment effect that is greater in the ISTp group than the IPTp group, where the 95% confidence interval does not include the point of no difference (RR value of 1).

Both modified intention-to-treat and per-protocol analyses will be undertaken for the efficacy analyses. The modified intention to treat analysis will be the primary analysis to assess superiority. In the absence of evidence for superiority, the prospectively defined non-inferiority margin will be 15% for adverse outcome or placental malaria in the intention to treat and per protocol populations (relative difference between endpoints of 15% (i.e. RR 0.85); e.g. 24.5% versus 28.8% for adverse birth outcome).

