## 17.4 Criteria for early termination of the trial

We will use an adaptive sequential design using one interim analysis half-way for assessing whether to stop the trial early due to safety, efficacy or futility. The Lan-DeMets alpha spending function with O'Brien-Fleming type boundaries will be used to preserve the overall type I error rate for efficacy at the 0.05 level. Interim analyses will be conducted by the independent Data Monitoring Committee (DMC) supported by the trial statistician. The DMC will provide the trial steering committee only with a recommendation to continue, terminate or modify the trial.

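### Two primary outcomes each get a plain 95% CI at full alpha, while the overall 0.05 in section 17.4 is not defined as per stratum or trial-wide and is not tied to the final test

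*Combined protocol and SAP*

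**What the plan says.** Section 9.1 sets one primary outcome per gravidity group: a composite of SGA, preterm birth and low birth weight in first and second pregnancies (G1-2), and malaria infection in third to fifth pregnancies (G3+).

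Section 17.3.3 names the G1-2 composite as the primary efficacy analysis and then adds: "Similar analyses will be undertaken for the additional primary outcome", meaning infection in G3+. It places the primary analysis at the level of the gravidity stratum. One superiority rule serves both outcomes: the effect must favour ISTp, "where the 95% confidence interval does not include the point of no difference (RR value of 1".

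Section 17.4 plans one interim analysis half-way, covering safety, efficacy and futility. The Lan-DeMets function with O'Brien-Fleming-type boundaries "will be used to preserve the overall type I error rate for efficacy at the 0.05 level".

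Section 17.1 sizes the G1-2 stratum "with an 90% power and a 2-sided significance level of 0.05" for a "25% difference between 40.3% in the control (IPTp) group and 30.2% in the intervention (ISTp) group", and concludes: "This would require 491 participants in each arm or 982 in total". For G3+ it says: "A reduction by 50% to 10.25% will require 213 women per arm or 426 in total", without giving a level or power.

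No section splits alpha between the two outcomes, puts them in a formal testing order, or says whether one win is enough. Section 17.4 does not say which outcome or stratum the boundary governs, and section 17.3.3 does not refer to the boundary.

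**The concern.** Two links are missing. The final decision rule is a plain 95% interval, although section 17.4 relies on a boundary that reserves some alpha for the interim look. And two primary tests, each at full alpha, stand beside a single promise about overall error.

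The difficulty arises if one stratum wins and the other does not. The plan does not say whether that is a positive trial, so the success rule could be settled after the results are known. Parts of the protocol treat the two outcomes as one question. Section 6.1 gives a single primary objective covering both. Section 7.2.1 describes one policy decision, whether to replace IPTp-SP. Section 7.2.9 expects an alternative to be offered to women of all gravidities if benefit is shown. On that reading a win in either stratum feeds the same claim, and the stated 0.05 does not hold across the pair. The monitoring committee also needs to know which outcome the boundary applies to before the interim look.

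**Working it through.** **1. Does each stratum use the full 0.05?** Reproduce the stated sizes with the continuity-corrected two-proportion formula:

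n0 = [1.960·√(2p̄(1−p̄)) + z_power·√(p1(1−p1) + p2(1−p2))]² / (p1−p2)², then n = (n0/4)·[1 + √(1 + 4/(n0·|p1−p2|))]².

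- G1-2: p1 = 0.403, p2 = 0.75 × 0.403 = 0.30225, power 90% (z = 1.282). n0 = 470.5 and n = 490.2, so 491 per arm, as stated.
- G3+: p1 = 0.205, p2 = 0.1025, with two-sided 0.05 and 80% power assumed (z = 0.842). n0 = 193.2 and n = 212.3, so 213 per arm, as stated.

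Both sizes match the full two-sided 0.05 in their own stratum.

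**2. The interim look, within one stratum.** Take half-way as information fraction t = 0.5.

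- Alpha spent: 4·[1 − Φ(2.2414/√0.5)] = 4·[1 − Φ(3.170)] = 0.00305, an interim boundary of |z| = 2.963.
- The final critical value c solves P(|Z1| ≥ 2.963 or |Z2| ≥ c) = 0.05, with correlation √0.5 between looks. This gives c = 1.969, nominal two-sided level 0.0490.
- With a plain 1.960 at the end instead, the error is 0.0510, an excess of 0.001.

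**3. Two strata.** The women are different and the randomization sequences are separate (section 17.2), so the tests are independent. The table assumes no effect in either stratum and that a win in either one counts.

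| Final rule | One stratum, two-sided | Either stratum, two-sided | One stratum, favouring ISTp | Either stratum, favouring ISTp |
|---|---|---|---|---|
| Boundary (1.969) | 0.0500 | 1 − 0.95² = 0.0975 | 0.0250 | 1 − 0.975² = 0.0494 |
| Plain 95% CI (1.960) | 0.0510 | 1 − 0.949² = 0.0994 | 0.0255 | 0.0503 |

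Going from one stratum to two adds 0.0475 (0.0975 − 0.0500). Dropping the boundary adds a further 0.0019 (0.0994 − 0.0975).

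**4. Timing of the look.** With a plain final interval, moving the look between information fractions 0.3 and 0.7 gives 0.0500 to 0.0541 per stratum and 0.0976 to 0.1054 across two.

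**5. Other success rules.** If each stratum supports only its own claim, each keeps about 0.05. If both must succeed, the joint error cannot exceed the per-stratum level.

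**6. Cost of adjusting.** With the interim look counted and power set at the design values, using 1.969 gives 89.9% (G1-2) and 79.9% (G3+). A Bonferroni split at 0.025 would cost far more: about 84% and 71% at the stated sizes. Restoring power would take 576 and 254 per arm, about 1,356 and 598 recruited after 15% loss (2 × 576/0.85 and 2 × 254/0.85).

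**The case against.** The best reply is that these are two questions. The women, endpoints and sample-size calculations differ, the randomization lists are separate, and section 7.2.9 gives each stratum its own rationale. Not adjusting across separate questions in disjoint populations is a recognised choice. The 0.05 in section 17.4 sits in the early-stopping section and may concern only repeated looks. Section 17.3.3 also gives the G1-2 composite some precedence by calling the other outcome additional. All of this is fair, and it rules out stating trial-wide inflation as a fact. It does not supply the missing rule: precedence in wording is not a testing order, and the word overall is left undefined.

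A second reply is that choosing Lan-DeMets spending already fixes the final critical value, so section 17.3.3 merely lacks a cross-reference. That is a reasonable reading, and on the opposite reading the excess is only about 0.001 per stratum. A reader might infer that the interim look is what drives the error up. It is not.

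A third reply concerns direction. A reader might take 0.0994 as a 10% chance of falsely declaring ISTp superior. The rule in section 17.3.3 counts only effects favouring ISTp, so that chance is about 0.05. The doubling relative to a single test stands on either scale.

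**Conclusion.** The point holds as a conditional one. The plan has two full-alpha primary tests, no success rule, and a final interval not tied to the boundary on which section 17.4 relies. If either stratum can carry a superiority claim, the familywise error is 0.0975 (boundary used) to 0.0994 (plain interval) two-sided, or about 0.05 in favour of ISTp against 0.025 for one test. The stronger reading, that the trial's true error simply is 0.10, is not supported. No section says that one win makes the trial positive, or that the 0.05 in section 17.4 covers both strata jointly.

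The figures assume an interim look at half information and independent strata. The level and power for G3+ are also assumptions, although the stated size fits them exactly. The design itself is not undermined. What is at stake is how a split result would be interpreted.

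**What to change.** 1. In section 17.3.3, state that final superiority uses the Lan-DeMets boundary: two-sided nominal level about 0.049, hence a 95.1% interval, recomputed at the actual information fraction. State in section 17.4 that the boundary applies within each gravidity stratum.
2. Choose one success rule before the interim look:
   - **Fixed order.** Test the G1-2 composite first, consistent with the precedence it already has. Treat G3+ infection as confirmatory only if that test succeeds. This holds the trial-wide two-sided error at 0.05 without splitting alpha.
   - **Separate claims.** Restate section 17.4 so that 0.05 is per gravidity stratum, limit each claim to its own stratum, and give the trial-wide two-sided error of 9.75%.

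No extra women are needed. The adjusted level costs at most about 0.2 percentage points of power. Under the fixed order, G3+ becomes descriptive if G1-2 fails. Under separate claims, the plan has to state a less favourable trial-wide error rate.

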### 17.3.4 Safety

Adverse events detected through passive surveillance and those requiring treatment will be grouped according to a pre-specified coding system and tabulated for each treatment arm on an intention-to-treat basis. Adverse events reported by women on DHA-PQ by active surveillance on day two after the first dose will be grouped according to a pre-specified coding system and tabulated for descriptive analysis only. Treatment emergent adverse events will be classified as those occurring within 24 hours after the first dose of a study drug. Adverse events that have missing onset dates will be considered as treatment emergent. The number and percentage of participants experiencing any adverse event, any serious adverse event, or any treatment emergent serious adverse event will be compared between intervention groups using Fishers Exact Test and Generalised linear models.

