Although minor events will be monitored in the ISTp arm, because of difficulties in identifying appropriate comparisons, there will be no systematic comparison of minor adverse event rates between trial arms. At each study intervention visit, participants will fall into three different categories: women with or without malaria infection taking SP; RDT-positive women taking DHA-PQ; and RDT-negative women taking no drug. The three groups will be different not only in the drug taken, but in their malaria status, knowledge of their malaria status, and their knowledge of the drug taken. Unbiased comparisons between groups are therefore not possible. Follow-up for symptomatic adverse events will therefore focus on serious adverse events, adverse events serious enough to be reported to the study clinics through passive surveillance or requiring treatment, and the tolerability of DHA-PQ assessed by women's self-reports on day three after the first dose.

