### 9.2.2 Safety outcomes

- 1. Severe cutaneous skin reaction in the mothers within 30 days of drug intake
- 2. Other serious adverse events in the mothers
- 3. Congenital malformations identified by six weeks after birth
- 4. Neonatal jaundice within 24 hours and at seven days
- 5. Laboratory test results outside of normal range

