## 15 Treatment of trial participants

### 15.1 The study intervention

Participants will receive one of the following two interventions during the second and third trimesters of pregnancy; provided at each of three scheduled visits between four and six weeks apart.

**IPTp-SP Group:** Treatment with a three tablets of sulphadoxine-pyrimethamine, each containing sulphadoxine (500 mg) and pyrimethamine (25 mg). This is the standard and only

drug of choice for IPTp in Africa. SP will be purchased from Durbin PLC in the UK and will be manufactured according to the GMP: Durbin PLC is a UK registered company - Company Registration Number: 3626868; Head Office: [name] T: [name], F: [name], [contact]

**ISTp-DP Group:** Screening for malaria using a combined HRP-2/ pLDH (*P. falciparum*/ pan-malaria) rapid diagnostic test (First Response® Malaria pLDH/HRP2 Combo Test, target antigen pLDH (pan); HRP2; Premier Medical Corporation Ltd, USA), and treatment if RDT-positive with dihydroartemisinin-piperaquine (Sigma Tau). Each tablet will contain 40 mg dihydroartemisinin and 320 mg piperaquine. Treatment will be given for three days, with the daily number of tablets depending on the weight of the woman to the nearest half tablet; dosage being 2 mg/kg/day of dihydroartemisinin and 16 mg/kg/day piperaquine.

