### 15.1.1 Administration of the study drugs

Women in either group who attend for a scheduled study appointment with fever and malaria confirmed by RDT or microscopy will be treated for malaria. In the case of women in the IPTp-SP group, case-management treatment will be given in place of the scheduled dose of SP, and this will be recorded on the CRF.

RDTs will be performed according to the manufacturer's instructions by the study staff at the clinic. Women in the ISTp group testing positive for either *P. falciparum* or other malaria species will be treated with DHA-PQ.

Participants receiving single-dose SP or the first dose of DHA-PQ will be given some clean water for swallowing the tablets. They will be observed swallowing the tablets and for thirty minutes afterwards. If vomiting occurs during this time the full dose will be repeated. If the participant vomits again after the repeated dose she will be discontinued from the trial and provided with second line therapy for malaria (CoArtem).

Participants receiving treatment with DHA-PQ will be given the remaining doses to take home, with instructions to take half the tablets the following day and half tablets the day after. Women with mobile or home telephones will be telephoned the next day to remind them to take their next dose. Women without mobile phone will be visited at home. All women regardless of mobile phone ownership will be visited by a fieldworker on the second day to check whether they have taken the tablets and whether they have had any problems.

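### The treatment-emergent rule in section 17.3.4 leaves most dosing unfollowed and admits undated events from women who took no study drug

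*Combined protocol and SAP*

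**What the plan says.** Section 17.3.4 sets both the window and its one exception. The window is: "Treatment emergent adverse events will be classified as those occurring within 24 hours after the first dose of a study drug". The exception is: "Adverse events that have missing onset dates will be considered as treatment emergent". The classification feeds a formal comparison, by Fisher's exact test and generalised linear models, in which the numbers with "any adverse event, any serious adverse event, or any treatment emergent serious adverse event will be compared between intervention groups".

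On dosing, section 15.1 says of DHA-PQ: "Treatment will be given for three days". Section 15.1.1 has the first dose observed in the clinic and sends the woman home with the rest, "with instructions to take half the tablets the following day and half tablets the day after". SP is a single-day treatment repeated at scheduled visits at least four weeks apart. Section 16.2.1 calls the interim-visit dose the second, and section 16.4.1 calls the final-visit dose the third or fourth.

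Two other statements bear on the point. Section 9.2.2 lists a separate outcome, "Severe cutaneous skin reaction in the mothers within 30 days of drug intake". Section 7.2.11 says that "there will be no systematic comparison of minor adverse event rates between trial arms", and expects only 155 to 233 of about 776 ISTp women to receive DHA-PQ.

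**The concern.** A treatment-emergent classification should pick out events that begin after exposure to a drug. Here exposure is repeated: three daily doses in a DHA-PQ course, possibly more than one course, and three or four SP administrations weeks apart. A window tied to a single first dose follows only a small part of it.

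The missing-date rule works in the opposite direction. It adds events whenever they occurred, and it is not restricted to women who had taken SP or DHA-PQ. Most ISTp women are expected to test negative throughout, so they have no dose to start a clock and can enter the count only through an undated record.

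The protocol says that DHA-PQ is less studied in pregnancy than SP and that this trial should add to what is known. A comparison of treatment-emergent SAEs with few events, or with events of mixed origin, could be read as reassurance that it cannot give.

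**Working it through.** The plan gives no figure for this definition, so there is none to reproduce. The check sets the window against the dosing schedule.

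**DHA-PQ within one course.** Doses fall at about 0, 24 and 48 hours (sections 15.1 and 15.1.1). The window runs from 0 to 24 hours. Only dose 1 of 3 has its following day inside it. Dose 2 falls at about the moment the window closes, and dose 3 about a day later. This holds whether the clock starts once per woman or once per course.

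**SP across visits.** Sections 16.2.1 and 16.4.1 number the doses second, then third or fourth, so the first dose is naturally the one at booking. The window then follows 1 of 3 or 1 of 4 administrations, and 2 of 3 or 3 of 4 are not followed at all.

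**Later DHA-PQ courses.** Sections 15.1.1 and 16.5 use first dose to mean day 1 of a course. Section 17.3.4 does not say which sense it intends.

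**Scale against a 30-day yardstick.** The 30 days come from section 9.2.2. They serve here only to show how short 24 hours is, because the plan does not apply them to treatment-emergent events.

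- One intake: 1/30 = 3.3%.
- One DHA-PQ course, from dose 1 to 30 days after dose 3: 24/(48 + 720) = 24/768 hours = 3.1%.
- Three SP doses 28 days apart: 28 + 28 + 30 = 86 days. Spaced 30 days or more: 3 × 30 = 90 days. One day counted is 1/86 = 1.2% to 1/90 = 1.1%.
- Four SP doses: 3 × 28 + 30 = 114 days, or 4 × 30 = 120 days. One day counted is 1/114 = 0.9% to 1/120 = 0.8%.
- If the 24 hours restarted at every one of three SP visits: 3/90 = 3.3% to 3/86 = 3.5%.

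Restarting the clock at each visit would settle the ambiguity, but the window would stay very short, and DHA-PQ doses 2 and 3 would still be left out.

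**Women with no clock.** Section 7.2.11 takes 20% to 30% of 776: 776 × 0.20 = 155 and 776 × 0.30 = 233. The remaining 776 − 233 = 543 to 776 − 155 = 621 ISTp women, or 70% to 80%, are expected to take no DHA-PQ. Section 17.3.4 still lets their undated events count as treatment emergent.

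**Would a longer window repair the between-arm test?** Assume 776 women per arm, three SP doses each, and one DHA-PQ course per treated woman, with 30 days of follow-up (2 + 30 = 32 days per course).

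- IPTp: 776 × 86 = 66,736 to 776 × 90 = 69,840 woman-days.
- ISTp: 155 × 32 = 4,960 to 233 × 32 = 7,456 woman-days.
- Ratio: 66,736/7,456 = 9.0 to 69,840/4,960 = 14.1. Two courses per treated woman would roughly halve it.

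A between-arm count of treatment-emergent events would then mainly reflect how much drug each arm received. Lengthening the window is therefore not enough, and the tabulation should also stop being a test between arms.

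**The case against.** The strongest reply is that little is lost. The sentence that compares treatment-emergent SAEs also compares any SAE, with no window. All adverse events are recorded with onset dates (section 18.2), and all SAEs go to the safety monitor and on to the Data Monitoring Committee (section 18.3). Treatment-emergent SAE is not listed among the safety outcomes in section 9.2.2 and is not a stated stopping criterion. All of this stands, and it limits the point to one secondary comparison.

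Four stronger readings are tempting, and the documents do not support them.

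- A reader might infer that the 24-hour rule contradicts the 30-day skin-reaction outcome and loses those events. It does not: that outcome is separate and carries its own window.
- A reader might infer that every later DHA-PQ course is certainly excluded. Sections 15.1.1 and 16.5 use first dose within a course, so this is ambiguous.
- A reader might infer that the comparison will show almost no events whatever the drugs do. The documents give no event rate to support that, and the missing-date rule pushes the count up.
- A reader might infer that home questioning of DHA-PQ women biases the test of any adverse event. Section 17.3.4 already makes those home-visit events descriptive only. What remains is that its last sentence does not repeat the restriction, and on its face it conflicts with section 7.2.11.

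It can also be said that undated SAEs should be rare, given the detailed reporting. That is likely, so the missing-date rule is the smaller part of the problem.

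**Conclusion.** The point holds for the definition and for the one comparison built on it. Section 17.3.4 leaves unfollowed two of the three doses in a DHA-PQ course on any reading. On the protocol's own numbering it also leaves out two of three or three of four SP doses. It admits undated events from the 70% to 80% of ISTp women expected to take no DHA-PQ. The treatment-emergent SAE comparison therefore does not measure events after drug exposure.

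The effect on counts cannot be stated, because the documents give no SAE rates. The 70% to 80% rests on the protocol's own expectation for positive tests. The 9- to 14-fold difference in follow-up time rests on the assumptions listed with it and argues against a between-arm test with a longer window. The efficacy analyses, the any-SAE comparison and the skin-reaction outcome are not affected.

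**What to change.** Reword section 17.3.4 as follows.

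1. Start the treatment-emergent window at each administration of SP or DHA-PQ, at any visit. For DHA-PQ, run it through the whole course plus a stated follow-up period. The 30 days already used in section 9.2.2 are one example.
2. Apply the missing-date rule only to women who took a study drug before the event was reported.
3. Tabulate treatment-emergent events, including SAEs, descriptively by drug actually taken. These are not randomised groups, and section 7.2.11 explains why they cannot be compared without bias.
4. Keep the between-arm intention-to-treat test for any SAE.
5. State in the last sentence that the comparison of any adverse event covers only events found passively or requiring treatment, in line with section 7.2.11 and the earlier sentences of section 17.3.4.

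The cost is a few sentences and some programming. Onset dates are already collected, and a window that opens with the clinic dose does not need exact times for the doses taken at home. The plan gives up its formal test of treatment-emergent SAEs. That is a small loss, because the any-SAE test remains.
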